## Background

Respiratory impairment is a common condition seen by healthcare service providers in primary healthcare, pulmonary medicine and other specialties. It is more common in older persons and the aging population (Vaz Fragoso & Gill 2012).

Respiratory diseases may lead to a significant reduction in the timed lung volume; the forced expiratory volume in 1 sec to forced vital capacity ratio (FEV_1_/FVC) is reduced and defines airflow limitations because of airway obstruction (Pellegrino et al. 2005). Respiratory diseases that lead to comparable reductions in the timed and untimed lung volumes include those that affect the chest wall and respiratory muscles, leading to a normal FEV_1_/FVC but reduced FVC (Pellegrino et al. 2005).

According to Fletcher (2019), respiratory symptoms such as dyspnoea have been found in a quarter to a third of the adult population with respiratory conditions such as chronic obstructive pulmonary disease (COPD). Chronic obstructive pulmonary disease is a group of progressive lung diseases commonly associated with emphysema, chronic bronchitis or both and are also associated with adverse outcomes such as increased disability and increased risk of death in the aging population (Agusti 2005; Soriano et al. 2005). Emphysema can lead to airway obstruction following the destruction of air sacs, while mucus build-up from inflammation can occur in bronchitis (Agusti 2005; Soriano et al. 2005).

Cystic fibrosis and idiopathic pulmonary fibrosis (IPF) are classified as restrictive airway diseases characterised by scarring of the lung tissues leading to a progressive decline in lung function (Liao et al. 2017). Interstitial lung disease (ILD) manifests as inflammatory, fibrotic infiltration of the alveolar walls resulting in the loss of lung tissue wall compliance (Nwosu et al. 2020). According to Anyabolu et al. (2013), the prevalence of IPF in the United States is 14 per 100 000; however, a scarcity of data is seen in the Nigerian population. A retrospective study between January 2015 and October 2018 by Nwosu et al. (2020) revealed that ILD accounted for 2.3% of respiratory conditions.

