Diagnosis of respiratory diseases is frequently established through spirometry because pathological confirmation is invasive and not routinely available. Hence, airflow obstruction or restrictive patterns collectively referred to as respiratory impairment is often detected through spirometry (Marcus et al. 2015). In summary, respiratory conditions such as asthma and COPD are classified as obstructive diseases, while those involving the chest wall, respiratory muscles, pleura or lung parenchyma are considered restrictive in nature (Vaz Fragoso & Gill 2012).

The diagnostic criteria that define spirometry respiratory impairment are often based on the Global Initiative for Obstructive Lung Disease (GOLD) (Quanjer et al. 1993). The threshold of < 0.70 for the spirometry ratio of FEV_1_ to FVC classifies normal spirometry, airflow obstruction or restriction in the adult population (Leivseth et al. 2013, Quanjer et al. 1993, Vaz Fragoso & Gill 2012). Airway obstruction is defined with an FEV_1_/FVC ratio of < 70% and an FVC of > 80% predicted, FEV_1_/FVC ratio of > 70% and an FVC of < 80% predicted for restrictive defects, while mixed defects are identified with FVC of < 80% predicted and an FEV_1_/FVC ratio of < 70% (Mathew et al. 2016; Uzma et al. 2008).

Based on the controversies surrounding the utilisation of Inspiratory Incentive Spirometry (IIS) and Expiratory Incentive Spirometry (EIS) in the management of respiratory impairments, our study was conceived to compare the effect of inspiratory and expiratory incentive spirometry exercise on the pulmonary parameters and quality of life (QoL) of patients with obstructive, restrictive or mixed respiratory impairments and to determine the most suitable intervention for the respective respiratory impairments.

According to Parshall et al. (2012), respiratory impairment is typically established by conducting a pulmonary function test (PFT) using a spirometer and subsequently categorised as airflow limitation (e.g. COPD or asthma) or airflow restriction (e.g. interstitial lung disease or heart failure). The criteria that define this airflow limitation are based on the GOLD (Rabe et al. 2007).

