## Significance of our study

The outcome of our study may establish the relationship between inspiratory and expiratory types of incentive spirometry in the management of obstructive, restrictive and mixed respiratory impairments.

Although studies have identified the general effect of incentive spirometry (IIS and EIS) in the management of respiratory conditions, none has been able to exclusively compare the impact of IIS with EIS on the different classes of respiratory impairments, thereby limiting the opportunity to identify the most suitable treatment modality for respiratory impairments. Our study is therefore designed to answer the following question.

What will be the effect of inspiratory and expiratory incentive spirometry on pulmonary function test (PFT), six-minute walk test (6MWT), Medical Research Council (MRC) dyspnoea scale and the Pulmonary Function Status and Disability Questionnaire-modified (PFSDQ-M) on patients with obstructive, restrictive or mixed respiratory impairments?

Thus, the aim of our study is to determine the effect of inspiratory and expiratory type of incentive spirometry on PFT, 6MWT, MRC dyspnoea scale score and PFSDQ-M score of patients with obstructive, restrictive or mixed respiratory impairments.

The specific objectives of our study are to determine:

The effect of inspiratory incentive spirometry on FEV_1_, FVC, FEV_1_/FVC, PEFR, 6MWT, MRC dyspnoea scale score and PFSDQ-M score of patients with obstructive, restrictive or mixed respiratory impairments.The effect of expiratory incentive spirometry on FEV_1_, FVC, FEV1/FVC, PEFR, 6MWT, MRC dyspnoea scale score and PFSDQ-M score of patients with obstructive, restrictive or mixed respiratory impairments.

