## Method

### Study Design

Our study will be a parallel 12-weeks randomised control trial, involving three groups; two intervention groups (IIS and EIS) and a parallel placebo control group of participants attending the respiratory clinic at the Lagos State University Teaching Hospital, Ikeja (LASUTH).

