### Participants

The participants will consist of male and female patients aged 40 years and above attending the respiratory clinic of Lagos State University Teaching Hospital, Ikeja, Lagos, Nigeria, West Africa, with spirometry confirmed obstructive, restrictive or mixed respiratory impairment for a period greater than 6 months.

The inclusion criteria are patients with COPD, IPF, ILD, cystic fibrosis, thoracic cage abnormalities (kyphosis, kyphoscoliosis, pectus carinatum or pectus excavatum) history of about or more than 6 months duration attending the respiratory clinic of LASUTH, Ikeja, Lagos. The respiratory condition of the selected participants must be spirometry confirmed to have resulted in an obstructive, restrictive or mixed respiratory airway impairment.

The exclusion criteria are patients who are on a cardiac pacemaker, supplemental oxygen therapy, those with cardiac conditions, patients with psychological impairments and patients with bronchial asthma.

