### Data analysis

The Statistical Package for Social Sciences (SPSS Inc, Chicago, Illinois, United Sates) version 26.0 for windows package programme will be used to analyse data. Descriptive statistics of mean, standard deviation, frequencies and percentages will be used to summarise the results. Bar charts, pie charts and histograms will be utilised for pictorial illustration. A multivariate analysis of variance (MANOVA) will be used to compare the outcome pulmonary function variables (FEV_1_, FVC, FEV_1_/FVC, PEFR) and QoL (6MWT, MRC dyspnoea scale score and PFSDQ-M score) among groups, while the Bonforreni’s *t*-test will be utilised for post hoc analysis to detect where significant changes occurred in the outcome variables. Dependent t-tests will be used to compare the pre- and post-test results within variables while independent t-tests will be used to compare the outcome variable among the study and control groups. The level of significance will be set at *p* ≤ 0.05.

The study does not potentially involve risk or harm, as all interventions can only be performed within the limit of the patient’s tolerance. However, participants may experience mild discomfort because of the exercise, including temporary muscle soreness, increased heart rate, blood pressure, sweating and dizziness. All necessary care will be in place to prevent the occurrence of any adverse event. However, in case of a report of serious adverse events (e.g. comorbidities, injuries, persistent excruciating pain, dizzy spells, headache, etc.) after the intervention or at any point during the trial, we would consider unblinding the participant to the intervention for their safety. Additionally, the participants will be instructed to report adverse events to the first author PI or the physiotherapist supervising their group. To ensure adequate supervision, participants per group to be attended in a day will be limited to a maximum of three. Arrangements will be made with the Accident and Emergency units of the research site to provide a standby medical team. The University of KwaZulu-Natal insurance scheme on clinical trials has fully covered participants in this type of study.

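### Uncontrolled pre/post t-tests stand beside controlled tests at the same significance level with no order of precedence, so a within-arm change can be reported as the effect of a therapy

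*Protocol article*

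**What the plan says.** The protocol article describes a 12-week randomised trial with "two intervention groups (IIS and EIS) and a parallel placebo control group" (Study Design). The Background gives a comparative purpose, "to compare the effect of inspiratory and expiratory incentive spirometry exercise on the pulmonary parameters". The aim that follows names no comparator: "the aim of our study is to determine the effect of inspiratory and expiratory type of incentive spirometry on PFT" (Significance of our study). Nor do the two specific objectives: "The effect of inspiratory incentive spirometry on FEV_1_, FVC, FEV_1_/FVC, PEFR, 6MWT, MRC dyspnoea scale score and PFSDQ-M score" and "The effect of expiratory incentive spirometry on FEV_1_, FVC, FEV1/FVC, PEFR, 6MWT, MRC dyspnoea scale score and PFSDQ-M score".

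The Data analysis section lists, in this order:

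- descriptive statistics;
- a MANOVA comparing the lung function and quality-of-life outcomes among groups, with Bonferroni post hoc tests;
- within-arm tests: "Dependent t-tests will be used to compare the pre- and post-test results within variables";
- in the second half of that same sentence, independent t-tests of the outcome variable between study and control groups;
- one significance level, p ≤ 0.05.

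The Sample size calculation is for the within-between interaction of a repeated-measures MANOVA. No section links a test to an objective or ranks the tests.

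**The concern.** A pre/post test within one arm asks whether the arm changed, not whether the therapy changed it. The article itself gives reasons why an arm might change without any therapy effect:

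- **Practice.** The six-minute walk test is repeated fortnightly. The Abstract has lung function measured before and after every procedure, and procedures run three times a week for 12 weeks.
- **Disease course.** The Background describes fibrotic disease as "characterised by scarring of the lung tissues leading to a progressive decline in lung function", and such patients are eligible. A therapy that only slowed decline could look inert or harmful in a pre/post test.

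The dependent t-tests are inferential, because descriptive statistics are listed separately. Of the planned tests, they are also the only ones that can be run on a single therapy with no other arm, so they fit the wording of the objectives most literally. With controlled and uncontrolled p-values side by side at the same level, whichever is favourable could be presented as the effect. The article hopes its findings may enter clinical guidelines and indicate which therapy suits which impairment. Within-arm p-values cannot support either use.

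**Working it through.** **1. Which test was the trial sized for?**

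Inputs (Sample size calculation): f(V) = 0.35, α = 0.05, power 0.80, k = 9 groups, m = 6 measurements, Pillai V, O'Brien-Shieh algorithm.

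- s = min(k − 1, m − 1) = min(8, 5) = 5
- numerator df = (k − 1)(m − 1) = 8 × 5 = 40
- denominator df = s(N − k − (m − 1) + s) = 5 × (51 − 9 − 5 + 5) = 210
- V = s·f²/(1 + f²) = 5 × 0.1225/1.1225 = 0.5457
- λ = f²·s·N = 0.1225 × 5 × 51 = 31.2375
- critical F = 1.4522; power from the noncentral F = 0.8011

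All of these match the article, and 51 is the smallest N that reaches 0.80. At the planned 54, power is 0.835. The powered test asks whether change over time differs between groups, so it is controlled. The dependent t-tests play no part in the calculation.

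**2. What does a pre/post test do when nothing works?**

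Group sizes (Abstract): 54 participants and six per therapy-by-impairment cell, hence 3 × 6 = 18 per therapy arm. The article gives neither an SD of change nor an expected drift. I assume the same drift in every arm, d in units of the SD of change, no therapy effect, and two-sided tests at 0.05.

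Paired t: rejection probability from the noncentral t with n − 1 df and noncentrality d√n.

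| Drift d | n = 18: d√n | n = 18: rejects | n = 6: d√n | n = 6: rejects |
|---|---|---|---|---|
| 0 | 0 | 5.0% | 0 | 5.0% |
| 0.2 | 0.849 | 12.6% | 0.490 | 6.9% |
| 0.3 | 1.273 | 22.5% | 0.735 | 9.3% |
| 0.5 | 2.121 | 51.6% | 1.225 | 17.1% |
| 0.8 | 3.394 | 89.2% | 1.960 | 35.6% |

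Between-arm t-test of change: the common drift cancels in the difference. Simulation with 100,000 runs for each of d = 0.3, 0.5 and 0.8 gave rejection of 4.9% to 5.0% at both group sizes.

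**3. Can the pre/post test also hide an effect?**

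Suppose a benefit of 0.5 SD is offset by a decline of 0.5 SD (assumed, as the article gives no rate of decline). Mean change in the treated arm is then 0 and the paired test rejects in 5%. The between-arm test has noncentrality 0.5 × √(n/2):

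- 18 per arm: 0.5 × √9 = 1.5, power 31%
- six per cell: 0.5 × √3 = 0.866, power 12%

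The controlled comparison is weak at these sizes, but it addresses the right quantity.

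**The case against.** A reader might infer that the objectives are to be answered by the dependent t-tests and that the control arm is discarded. The documents do not support this. The sentence that plans the dependent t-tests goes on to plan independent t-tests against the control groups. The sentence before it plans a MANOVA among groups, the Abstract names a repeated MANOVA, and the trial is sized on the within-between interaction. No section calls the dependent t-tests primary or treats within-arm significance as proof of effect. Nor does any section propose to set a significant therapy arm against a non-significant control arm.

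A reader might also expect a calculable regression to the mean, since the condition "must be spirometry confirmed to have resulted in an obstructive, restrictive or mixed respiratory airway impairment" and spirometry values are outcomes as well. The documents do not support a figure. The Background defines obstruction by FVC above 80% predicted, and restrictive and mixed defects by FVC below 80%, so selection on FVC runs in opposite directions within an arm. It is also not stated that the qualifying test is the baseline measurement.

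Two further points stand. The drift sizes are assumptions, and if results are read by impairment class the smaller n = 6 figures apply. An order of precedence among tests is often left to an analysis plan that is not shown. This last point does not dispose of the matter: the article positively fixes an inferential pre/post test that cannot estimate a therapy effect, under objectives that omit the comparator.

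**Conclusion.** The concern holds in a limited form. The plan contains a comparator and controlled analyses, but it gives an uncontrolled test the same standing and does not say which of them carries the claim of effect. Under an assumed common drift of 0.3 to 0.5 SD of change and no therapy effect, a single paired test gives a false positive in 23% to 52% at 18 per arm and 9% to 17% at six per cell, against about 5% for a between-arm test of change. These rates hold per outcome and per arm and depend wholly on the assumed drift; with none, the paired test keeps its 5%. Masking of a benefit by decline is possible in principle, but its size over 12 weeks cannot be judged from the article.

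A related gap lies in the controlled test. The independent t-test is applied to an outcome variable that is not specified as post value or change, and it adjusts for neither baseline nor impairment class.

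**What to change.** In the Data analysis section:

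- State that the effect of IIS, and likewise of EIS, is the randomised contrast with control in 12-week change, adjusted for the baseline value and impairment class. The group-by-time interaction already used in the Sample size calculation would also serve. Only this comparison supports a claim of effect.
- Let that contrast replace the unadjusted independent t-test.
- Report within-arm changes only descriptively, as means with 95% confidence intervals, and remove the dependent t-tests as tests of effect.
- Define pre and post as baseline and week 12, since lung function is also measured before and after each session.

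In the aim and specific objectives, add the words that name control as the comparator.

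The cost is wording only: no added patients, visits or measurements. The downside is that within-arm significance can no longer be quoted as evidence of effect, and the evidence then rests on a contrast with modest power (31% for a difference of 0.5 SD of change at 18 per arm, before any gain from baseline adjustment).

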**Method:**

Fifty-four patients aged 40 years and above with obstructive, restrictive or mixed respiratory impairments attending the respiratory clinic at the Lagos State University Teaching Hospital, Ikeja (LASUTH), will be recruited and assigned to three groups of 18 participants based on the class of respiratory impairment. Participants in each category of respiratory impairment will be subdivided into three groups. A final group of six participants per class of impairment will participate in the experiment. Our study will be a double-blind, randomised control trial with two intervention groups and one parallel placebo control group. Pulmonary function will be assessed before and after every procedure while the six-minute walk test (6MWT), Medical Research Council dyspnoea scale and the Pulmonary Functional Status and Dyspnea Questionnaire-Modified will be assessed fortnightly during our study. Data will be analysed using descriptive and inferential statistics and a repeated MANOVA; *p* < 0.05.

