### Sample size calculation

The pulmonary function test is the primary outcome of interest for our study and the expected clinically relevant difference for obstructive restrictive and mixed impairment using LLN and GLI reference equation as proposed by Quanjer et al. (1993). Therefore, the sample size (*n*) will be determined using G-Power statistics software (stats.oarc.ucla.edu). The power is selected at 95% = 0.95, confidence level at 5% = 0.05 and effect size of 0.35 (Figure 1), namely:

**F-tests – MANOVA:** Repeated measures, within-between interaction

**Options:** Pillai V, O’Brien-Shieh Algorithm

**Analysis:** A priori: Compute required sample size

**Input:** Effect size f(V) = 0.35

    α err prob = 0.05

    Power (1-β err prob) = 0.8

    Number of groups = 9

    Number of measurements = 6

**Output:** Non-centrality parameter λ = 31.2375000

     Critical F = 1.4522092

     Numerator degree of freedom (*df*) = 40.0000000

     Denominator df = 210

     Total sample size = 51

     Actual power = 0.8010637

     Pillai V = 0.5456570

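### The study-versus-control t-tests leave out the measured pre-treatment value and depart from the repeated-measures analysis on which the trial was sized

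*Protocol article*

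**What the plan says.** The Data analysis section gives three layers of testing.

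- Omnibus: "A multivariate analysis of variance (MANOVA) will be used to compare the outcome pulmonary function variables" and the quality-of-life measures among groups, followed by Bonferroni post hoc t-tests.
- Within groups: "Dependent t-tests will be used to compare the pre- and post-test results within variables".
- Study against control: "independent t-tests will be used to compare the outcome variable among the study and control groups".

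No covariate, ANCOVA or between-group test of change is named there or anywhere else in the article.

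The Abstract describes the omnibus analysis differently: "Data will be analysed using descriptive and inferential statistics and a repeated MANOVA". The Sample size calculation section uses the same form, a MANOVA specified as "Repeated measures, within-between interaction", with nine groups and six measurements.

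On the data available, the Abstract says "Pulmonary function will be assessed before and after every procedure", so a value before the first session exists for the primary outcome. The walk test, the MRC scale and the PFSDQ-M "will be assessed fortnightly during our study". On group size, the Abstract says "A final group of six participants per class of impairment will participate in the experiment", that is, six per therapy within each class and 54 in total.

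**The concern.** Participants are of both sexes, aged 40 and above, with conditions from COPD to chest-wall deformity. People therefore differ a good deal in FEV1, FVC, PEFR and walking distance before any treatment. Allocation is by ballot within impairment class, and no balancing on severity is described.

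A t-test that compares final values puts this stable spread into its error term, although the trial has already measured it. With cells of six, or arms of 18 if the classes are pooled, two things follow. The test detects only large differences. And in any one realised allocation, a chance gap at baseline carries through to the end of treatment, where it can look like a therapy effect or hide one.

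The t-tests also answer the main question with a method other than the one used to justify the sample size. The repeated-measures interaction removes each person's own level; an independent t-test of an outcome value does not.

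**Working it through.** **The plan's own figure.** Inputs from the Sample size calculation section: f(V) = 0.35, α = 0.05, power 0.80, 9 groups, 6 measurements. With s = min(9 − 1, 6 − 1) = 5:

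- λ = s·f²·N = 5 × 0.1225 × 51 = 31.2375
- df1 = 8 × 5 = 40; df2 = 5 × (51 − 9) = 210
- V = s·f²/(1 + f²) = 0.6125/1.1225 = 0.5457
- critical F = 1.4522; power = 0.8011

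All match the printed output, and 51 is the smallest N that reaches 0.80. The sample size is therefore that of a group-by-time test, not of the t-tests.

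**Inputs for the t-tests.** Group size is 6 per cell or, with classes pooled, 18 per arm; the article does not say which applies. α = 0.05, taken as two-sided because the sidedness is not stated. SD is set to 1. The correlation r between the pre-treatment and week-12 values is not given for any outcome, so a range is used. The only repeat-measurement correlation quoted for a trial outcome is 0.83, a test-retest value for PFSDQ-M dyspnoea.

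**Chance imbalance.** The SD of the difference in baseline means is √(2/n).

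- n = 6: √(2/6) = 0.577; P(gap > 0.5 SD) = 2[1 − Φ(0.5/0.577)] = 0.386
- n = 18: √(2/18) = 0.333; P(gap > 0.5 SD) = 2[1 − Φ(0.5/0.333)] = 0.134

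**Precision.** The variance factor is 1 for the unadjusted test, with 2n − 2 df. With baseline as covariate it is (1 − r²)(1 + 1/(2n − 4)), with 2n − 3 df. The second bracket is the cost of estimating the slope: 1.125 at n = 6 and 1.031 at n = 18. Example at n = 6, r = 0.7: 0.51 × 1.125 = 0.574. Power is from the noncentral F with noncentrality d²/(2 × factor/n).

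| r | Factor, 6 v 6 | Detectable at 80%, 6 v 6 | Factor, 18 v 18 | Power for 0.5 SD, 18 v 18 |
|---|---|---|---|---|
| unadjusted | 1 | 1.80 SD | 1 | 31% |
| 0.3 | 1.024 | 1.84 SD | 0.938 | 32% |
| 0.5 | 0.844 | 1.67 SD | 0.773 | 38% |
| 0.7 | 0.574 | 1.38 SD | 0.526 | 52% |
| 0.8 | 0.405 | 1.16 SD | 0.371 | 67% |
| 0.83 | 0.350 | 1.08 SD | 0.321 | 73% |
| 0.9 | 0.214 | 0.84 SD | 0.196 | 91% |

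One minus the factor is the share of precision (inverse variance) given up by not adjusting. At 6 v 6 this is none at r = 0.3, 16% at 0.5, 43% at 0.7, 60% at 0.8 and 79% at 0.9. It passes one half when (1 − r²) × 1.125 < 0.5, that is, r above about 0.75.

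**Error rate.** In 40,000 simulated 6 v 6 trials with no therapy effect and r = 0.83, the unadjusted test rejected in about 18% of those with a baseline gap of 0.9 to 1.2 SD, and in about 0.3% of those with a gap below 0.1 SD. Averaged over all allocations the test keeps its nominal 5%.

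**The case against.** **The plan is not blind to baseline.** The Abstract and the Sample size calculation section specify a repeated-measures MANOVA, and its group-by-time interaction removes each person's stable level. This stands. A reader might infer that every between-group analysis ignores baseline, and the documents do not support that. But the omnibus interaction over nine groups does not estimate therapy against control. The test named for that contrast is the independent t-test, and the Data analysis section does not repeat the repeated-measures form.

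**The response variable is not spelled out.** The t-tests could be run on change from baseline, and an article may leave that to a fuller document. Nothing says so, however, and the same sentence assigns the pre-test value to paired tests only. If change is meant, much of the loss is recovered at high r (6 v 6 detectable difference 1.39 SD at r = 0.7, 0.80 SD at 0.9). At low r it is worse than no adjustment (2.13 SD at r = 0.3).

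**Most of the precision may not be lost.** A reader might infer that it is. That needs r above about 0.75 at 6 v 6, and the documents give no such correlation. The 0.83 is a test-retest figure for one questionnaire scale, not a 12-week correlation for lung function.

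**Randomisation already covers imbalance.** This is right for the overall error rate: chance gaps are part of the t-test's standard error. A claim of inflated type I error would be wrong. What remains is bias given the imbalance actually seen, and low power.

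**Cells of six are one reading.** The t-tests may pool classes, in which case the 39% becomes 13%. The gain from adjustment remains at 18 v 18.

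**Conclusion.** The point holds in a limited form. The only test named for study versus control is an independent t-test with no baseline term, although the pre-treatment value of the primary outcome is collected, and this is out of step with the analysis behind the sample size.

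The size of the loss depends on an undocumented r: nothing to gain at about 0.3 with six per cell, a modest gain at 0.5, and a large one from 0.7 upward. The figures assume a t-test of final values, a two-sided 5% level, equal variances and a linear relation with baseline. It is a cheap improvement to a stated method and does not show that the trial is invalid.

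**What to change.** Replace the independent t-tests with one model per outcome: an ANCOVA at week 12, or a mixed model on the repeated measurements. Include therapy, impairment class, therapy-by-class and the participant's own pre-randomisation value of that outcome. The interaction is needed because the trial asks which therapy suits which impairment. Report adjusted therapy-versus-control differences with 95% confidence intervals, overall and by class. Use an ordinal model for the five-grade MRC scale.

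Bring the Abstract, the Sample size calculation and the Data analysis sections into line on whether the omnibus analysis is the repeated-measures form.

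Confirm that the first walk test, MRC and PFSDQ-M assessments precede treatment. Fortnightly assessment over 12 weeks from week 0 to week 12 gives 12/2 + 1 = 7 occasions, whereas the sample size input has six, so one end may be missing.

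Cost: one error degree of freedom per outcome, which in the ANCOVA with nine cells and 54 participants means 44 instead of 54 − 9 = 45. There is a slight loss of precision only if r is about 0.3 or lower. For lung function no new data are needed.
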